#### **Approval by the Institutional Review Board or Ethics Committee**

Sampling for the RCR is contingent upon the review and approval of the exploratory research and the RCR portion of the Informed Consent Form by each site's Institutional Review Board or Ethics Committee (IRB/EC) and, if applicable, an appropriate regulatory body. If a site is not granted approval for RCR sampling, this section of the protocol will not be applicable at that site.

#### **Sample Collection**

Optional plasma, RNA, and DNA RCR samples will be collected according to the Schedule of Assessments (see [Appendix A](#)).

For all samples, dates of consent and specimen collection should be recorded on the associated RCR page of the eCRF. For sampling procedures, storage conditions, and shipment instructions, see the Sample Handling and Logistics Manual.

Roche Clinical Repository specimens will be destroyed no later than 15 years after the date of final closure of the associated clinical database. The RCR storage period will be in accordance with the IRB/EC-approved Informed Consent Form and applicable laws (e.g., health authority requirements).

The dynamic biomarker specimens will be subject to the confidentiality standards described in Section 8.4. The genetic biomarker specimens will undergo additional processes to ensure confidentiality, as described below.

### **Confidentiality**

Given the sensitive nature of genetic data, Roche has implemented additional processes to ensure patient confidentiality for RCR specimens. Upon receipt by the RCR, each specimen is "double-coded" by replacing the patient identification number with a new independent number. Data generated from the use of these specimens and all clinical data transferred from the clinical database that are considered relevant are also labeled with this same independent number. A "linking key" between the patient identification number and this new independent number is stored in a secure database system. Access to the linking key is restricted to authorized individuals and is monitored by audit trail. Legitimate operational reasons for accessing the linking key are documented in a standard operating procedure. Access to the linking key for any other reason requires written approval from the Pharma Repository Governance Committee and Roche's Legal Department, as applicable.

Data generated from RCR specimens must be available for inspection upon request by representatives of national and local health authorities, and Roche monitors, representatives, and collaborators, as appropriate.

Patient medical information associated with RCR specimens is confidential and may only be disclosed to third parties as permitted by the Informed Consent Form (or separate authorization for use and disclosure of personal health information) signed by the patient, unless permitted or required by law.

Data derived from RCR specimen analysis on individual patients will generally not be provided to study investigators unless a request for research use is granted. The aggregate results of any research conducted using RCR specimens will be available in accordance with the effective Roche policy on study data publication.

Any inventions and resulting patents, improvements, and/or know-how originating from the use of RCR data will become and remain the exclusive and unburdened property of Roche, except where agreed otherwise.

### **Consent to Participate in the RCR**

The Informed Consent Form will contain a separate section that addresses participation in the RCR. The investigator or authorized designee will explain to each patient the objectives, methods, and potential hazards of participation in the RCR. Patients will be told that they are free to refuse to participate and may withdraw their specimens at any time and for any reason during the storage period. A separate, specific signature will be required to document a patient's agreement to provide optional RCR specimens.

Patients who decline to participate will check a “no” box in the appropriate section and will not provide a separate signature.

The investigator should document whether or not the patient has given consent to participate by completing the RCR Research Sample Informed Consent eCRF.

In the event of an RCR participant's death or loss of competence, the participant's specimens and data will continue to be used as part of the RCR research.

### **Withdrawal from the RCR**

Patients who give consent to provide RCR specimens have the right to withdraw their specimens from the RCR at any time for any reason. If a patient wishes to withdraw consent to the testing of his or her specimens, the investigator must inform the Medical Monitor in writing of the patient's wishes using the RCR Subject Withdrawal Form and, if the trial is ongoing, must enter the date of withdrawal on the RCR Research Sample Withdrawal of Informed Consent eCRF. The patient will be provided with instructions on how to withdraw consent after the trial is closed. A patient's withdrawal from Study NV27780 does not, by itself, constitute withdrawal of specimens from the RCR. Likewise, a patient's withdrawal from the RCR does not constitute withdrawal from Study NV27780.

### **Monitoring and Oversight**

RCR specimens will be tracked in a manner consistent with Good Clinical Practice by a quality-controlled, auditable, and appropriately validated laboratory information management system to ensure compliance with data confidentiality as well as adherence to authorized use of specimens as specified in this protocol and in the Informed Consent Form. Roche monitors and auditors will have direct access to appropriate parts of records relating to patient participation in the RCR for the purposes of verifying the data provided to Roche. The site will permit monitoring, audits, IRB/EC review, and health authority inspections by providing direct access to source data and documents related to the RCR samples.

In addition to an internal review body, an independent Science and Ethics Advisory Group—consisting of experts in the fields of biology, ethics, sociology, and law—will advise Roche regarding the use of RCR specimens and on the scientific and ethical aspects of handling genetic information.

## **4.5.2 Timing of Study Assessments**

### **4.5.2.1 Screening and Pretreatment Assessments**

Written informed consent for participation in the study must be obtained before performing any study-specific screening tests or evaluations. Informed Consent Forms for enrolled patients and for patients who are not subsequently enrolled will be maintained at the study site.

Screening evaluations will be performed between 8 weeks before and 1 day before the patient is randomized. All screening evaluations must be completed and reviewed to confirm that patients meet all eligibility criteria before randomization. The investigator will maintain a screening log to record details of all patients screened and to confirm eligibility or record reasons for screening failure, as applicable.

See [Appendix A](#) for the schedule of screening and pretreatment assessments.

#### **4.5.2.2 Assessments During Treatment**

See [Appendix A](#) for the Schedule of Assessments performed during the treatment period.

#### **4.5.2.3 Assessments at Study Completion/Early Termination Visit**

Any patient who prematurely discontinues all study drugs should return for the PW Visit as soon as possible after the last dose of study medication. Additional requirements exist for patients who have unquantifiable HCV RNA levels at the time of premature study drug discontinuation (see [Appendix A](#)).

- If a patient stops Pegasys, all study medications must be discontinued.
- If a patient stops one DAA (either RO5024048 or boceprevir), the patient may remain on the other DAA (either RO5024048 or boceprevir) plus Pegasys/Copegus.
- If both RO5024048 and boceprevir are stopped, the patient may remain on Pegasys/Copegus.
- If a patient stops Copegus, all study medications must be discontinued.
- Patients should not be treated with a single DAA (either RO5024048 or boceprevir) and Pegasys or with Pegasys monotherapy.
- In other circumstances, the investigator should consult with the Sponsor.

See [Appendix A](#) for the Schedule of Assessments performed at the Study Completion/Early Termination Visit.

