### **5.4.3            Reporting Requirements for Pregnancies**

#### **5.4.3.1        Pregnancies in Female Patients**

Female patients of childbearing potential will be instructed to immediately inform the investigator if they become pregnant during the study or within 6 months after the study or according to the locally approved label for Copegus after the last dose of study drug. A Pregnancy Report eCRF should be completed by the investigator immediately (i.e., no more than 24 hours) after learning of the pregnancy and submitted via the EDC system. A pregnancy report will automatically be generated and sent to Roche Safety Risk Management. Pregnancy should not be recorded on the AE eCRF. The investigator should discontinue Copegus and counsel the patient, discussing the risks of the pregnancy and the possible effects on the fetus. Monitoring of the patient should continue until conclusion of the pregnancy.

In the event that the EDC system is unavailable, a Pregnancy Report Worksheet and Pregnancy Fax Coversheet should be completed and faxed to Roche Safety Risk Management or its designee immediately (i.e., no more than 24 hours) after learning of the pregnancy, using the fax numbers provided to investigators (see “Protocol Administrative and Contact Information and List of Investigators”).

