##### **Dose delayed by $\geq 7$ days**

The investigator may reintroduce Pegasys at any time and, if necessary, dose the patient every fifth or sixth day until the patient resumes weekly dosing on his/her usual scheduled day.

Moderate or severe adverse reactions (clinical and/or laboratory) may require a dose reduction of Pegasys. Decremental reductions should be uniform across centers and patients. Toward this end, downward reductions should follow the guidelines shown in [Table F1](#).

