**Table F4**  
Dose Adjustment for Low Hemoglobin

|                                                              | One Level Adjustment for Copegus if: | Withhold Copegus if:  |
|--------------------------------------------------------------|--------------------------------------|-----------------------|
| In patients without
significant cardiovascular
disease | Hemoglobin < 10 g/dL                 | Hemoglobin < 8.5 g/dL |

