## Appendix F

### Dose Modifications, Interruptions, and Delays (cont.)

**Table F5**  
General Copegus Dose-Reduction Scheme

|                       | Baseline Body Weight                       |                                            |
|-----------------------|--------------------------------------------|--------------------------------------------|
|                       | ≥ 75 kg                                    | < 75 kg                                    |
| Full Copegus dose     | 1200 mg/day
(AM: 3 tabs;
PM: 3 tabs) | 1000 mg/day
(AM: 3 tabs;
PM: 2 tabs) |
| One-level reduction   | 1000 mg/day
(AM: 3 tabs;
PM: 2 tabs) | 800 mg/day
(AM: 2 tabs;
PM: 2 tabs)  |
| Two-level reduction   | 800 mg/day
(AM: 2 tabs;
PM: 2 tabs)  | 600 mg/day
(AM: 2 tabs;
PM: 1 tab)   |
| Three-level reduction | 600 mg/day
(AM: 2 tabs;
PM: 1 tab)   | 400 mg/day
(AM: 1 tab;
PM: 1 tab)    |

At the discretion of the investigator, patients who experience a substantial hemoglobin decrease during treatment should have weekly or biweekly hematologic testing and clinical evaluation. Patients who have > 3 g/dL decrease from baseline in their Hgb concentration should have an appropriate work-up for anemia—including reticulocyte count—and a search for sources of bleeding.

If deemed necessary by the investigator, patients should be assessed at a minimum every 2 weeks until the AE is resolved or the patient is stable. Persistent adverse reactions may require two- or three-level dose reductions or necessitate that the dose be temporarily withheld.

Once the Copegus dose has been reduced or withheld for an adverse reaction, an attempt may be made to restart Copegus and/or increase the dose if the event has resolved or improved, at the discretion of the investigator. The Copegus dose should be increased in 200-mg increments by increasing the number of tablets taken daily in a stepwise manner until the desired level is achieved. It is not recommended to escalate to the fully prescribed dose of Copegus.

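### Withholding Copegus for low haemoglobin under Appendix F leaves some patients, chiefly Arm B in Weeks 24–48, on a regimen that Section 4.5.2.3 disallows

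*Protocol*

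**What the plan says.** Section 4.5.2.3 concerns the early termination visit and begins: "Any patient who prematurely discontinues all study drugs should return for the PW Visit as soon as possible after the last dose of study medication". Its bullets then set rules for partial discontinuation:

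- For interferon: "If a patient stops Pegasys, all study medications must be discontinued".
- For ribavirin: "If a patient stops Copegus, all study medications must be discontinued".
- A patient who stops one DAA may stay on the other with Pegasys/Copegus, and a patient who stops both may stay on Pegasys/Copegus.
- "Patients should not be treated with a single DAA (either RO5024048 or boceprevir) and Pegasys or with Pegasys monotherapy".
- Other circumstances go to the Sponsor.

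Appendix F handles the same drugs by interruption. In Table F4 the column headed "Withhold Copegus if" gives haemoglobin below 8.5 g/dL, for patients without significant cardiovascular disease. The text after Table F5 accepts temporary withholding of Copegus and adds that "an attempt may be made to restart Copegus and/or increase the dose if the event has resolved or improved", at the investigator's discretion. Table F3 withholds Pegasys at a neutrophil count below 500 cells/mm³ and reinstates it above 750. A Pegasys dose delayed by 6 days is withheld for that week. After a delay of 7 days or more, "The investigator may reintroduce Pegasys at any time".

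Section 4.1 limits RO5024048 to 24 weeks in both arms. Boceprevir and Pegasys/Copegus run for 24 weeks in Arm A and 48 weeks in Arm B.

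**The concern.** The two sets of rules apply to the same patients but do not refer to each other. Section 4.3.2 sends sites to Appendix F for interruptions, and the anaemia entry in Appendix G sends them to Tables F4 and F5 and the boceprevir package insert. Neither appendix points to the bullets in Section 4.5.2.3, which sit in a section on visit timing.

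The situation is foreseeable. Section 5.1 names anaemia as a significant adverse event of boceprevir and haemolytic anaemia as one of Pegasys/Copegus.

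If the site follows Table F4 and leaves the other drugs running, the patient may be on a regimen that Section 4.5.2.3 says should not be used. If the site treats the event as a stop under Section 4.5.2.3, all drugs end and the patient becomes a premature withdrawal. The SVR-12 window, 8–20 weeks after the last day of study drug (Section 6.4.1), then runs from that earlier date. The choice therefore affects both the treatment received and the timing of the primary endpoint. Because the clearest case arises only in Arm B, it may affect the two groups unequally.

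**Working it through.** The point rests on comparing passages; the protocol gives no figure of its own to reproduce for it.

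**Step 1. What remains when Copegus alone is withheld under Table F4.** Inputs are the durations in Section 4.1, the Table F4 action, and the permitted partial regimens in Section 4.5.2.3.

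| Situation | Drugs left | Ruled out by the single-DAA/Pegasys bullet? |
|---|---|---|
| Weeks 0–24, either arm, both DAAs running | RO5024048 + boceprevir + Pegasys | No; two DAAs plus Pegasys is not named |
| Arm B, Weeks 24–48, RO5024048 completed | boceprevir + Pegasys | Yes |
| Any patient already off one DAA, the other still running | one DAA + Pegasys | Yes |
| Any patient with no DAA still running | Pegasys | Yes |

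The last three rows are states that the protocol itself creates or permits. The bullet is worded in terms of what the patient is treated with, so these conflicts do not depend on what counts as a stop. It has no exception for temporary withholding. Both instructions could be met only if the remaining drugs were also paused or ended, and Table F4 directs neither.

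**Step 2. Whether the Grade 4 rule settles it.** Section 4.6.1.1 stops all drugs for a confirmed, clinically significant Grade 4 laboratory abnormality. In Appendix I, haemoglobin of 7.0–8.9 g/dL is Grade 3 for HIV-negative adults, and Grade 4 begins below 7.0. From 7.0 to just under 8.5 g/dL, Table F4 applies and the Grade 4 rule does not.

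**Step 3. When withholding becomes stopping.** Section 4.5.2.3 does not define a stop. Appendix F gives no maximum interruption for Copegus, and allows Pegasys to be reintroduced after a delay of any length. No point is fixed at which an interruption becomes a stop, and neither place says what happens to the other drugs meanwhile.

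**Step 4. Scale.** With 30 patients per group (Section 6.1), one patient's SVR-12 status is 1/30 = 3.3 percentage points. For context, the planned 90% interval half-width is 1.645 × √(0.5 × 0.5/30) = 15.0 points, which agrees with the protocol's ±15%.

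**The case against.** The strongest reply is that a stop in Section 4.5.2.3 means a permanent one. The bullets stand under the early termination heading. The protocol uses other words for temporary action, Section 4.5.1.2 records interruptions apart from premature withdrawals, and Table F2 has its own wording for permanent discontinuation of Pegasys. Reading every withheld dose as a stop would also empty the Pegasys withhold-and-resume rules. This reply largely stands. A reader might infer that every withholding of Copegus or Pegasys contradicts Section 4.5.2.3; the documents do not support that. The reply does not reach the single-DAA/Pegasys bullet, and it leaves the length of an interruption open.

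Other stronger readings also fail:

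- **That withholding always continues a disallowed regimen.** With both DAAs running it does not. Withholding Pegasys leaves DAA(s) plus Copegus, which the bullet does not name.
- **That one haemoglobin value triggers withholding of either drug.** Table F4 concerns Copegus; Pegasys is withheld for neutrophils, platelets or delayed doses.
- **That Appendix F orders Copegus to be restarted.** It permits an attempt.
- **That the pregnancy rule is a further conflict.** Section 5.4.3.1 says "The investigator should discontinue Copegus and counsel the patient"; Section 4.5.2.3 then says what follows for the other drugs. The two work in sequence.

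Referral to the Sponsor does not resolve the conflict, because that bullet covers other circumstances and these regimens are named ones. The boceprevir package insert, to which Appendix G refers, was not available for this review and may bear on how boceprevir is handled in anaemia. It would not remove the disagreement between the two protocol passages.

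**Conclusion.** The point holds for a defined set of patients: Arm B in Weeks 24–48, and any patient already off one or both DAAs. For them, withholding Copegus as Table F4 directs while the rest of the regimen continues leads to treatment that Section 4.5.2.3 says should not be given. That is a contradiction between treatment rules, not merely missing detail. The undefined stop is a secondary ambiguity, with the wording elsewhere favouring a permanent stop.

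The only firm figure is 3.3 percentage points of SVR-12 per patient in a group of 30. A reader might multiply an assumed anaemia rate into a shift in SVR-12. The protocol gives no rate for haemoglobin below 8.5 g/dL, and such a product would be a ceiling, since it requires every affected patient's outcome to change with the reading chosen. That sites would act differently is a risk created by the wording, not something the documents state. SVR-12 remains defined under either reading, and no hypothesis test depends on it.

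**What to change.** Reconcile Section 4.5.2.3 with the Appendix F rules on Pegasys delays, Table F3, Table F4 and the Copegus restart text. The amended wording should state:

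1. whether a stop of Copegus or Pegasys includes temporary withholding;
2. when an interruption counts as a stop;
3. how the single-DAA/Pegasys-monotherapy bullet applies while Copegus is withheld, with Arm B Weeks 24–48 and patients already off one or both DAAs addressed explicitly.

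Cross-references between Section 4.5.2.3 and Appendices F and G would keep the places aligned. Which rule applies is for the sponsor's clinical team; the statistical need is that all places give the same instruction. The cost is wording in one amendment and a memo to sites, with no added visits, tests or patients.

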#### **4.5.2.4 Follow-Up Assessments**

After the Study Completion/Early Termination Visit, AEs should be followed as outlined in Section [5.5](#) and [5.6](#).

See [Appendix A](#) for the schedule of follow-up assessments.

## **4.6 PATIENT, STUDY, AND SITE DISCONTINUATION**

### **4.6.1 Patient Discontinuation**

The investigator has the right to discontinue a patient from any study drug or withdraw a patient from the study at any time. In addition, patients have the right to voluntarily discontinue study drugs or withdraw from the study at any time for any reason. Reasons for discontinuation of a study drug or withdrawal from the study may include, but are not limited to, the following:

- Patient withdrawal of consent at any time
- Any medical condition that the investigator or Sponsor determines may jeopardize the patient's safety if he or she continues in the study
- The investigator or Sponsor determines it is in the best interest of the patient.

#### **4.6.1.1 Discontinuation from Study Drug**

All study medications should be stopped for individual patients for any of the following reasons:

- Hepatitis C virus RNA titer > 100 IU/mL by Week 24
- Quantifiable HCV RNA at Week 24
- Hepatitis C virus RNA virologic breakthrough before the end of treatment with boceprevir and/or RO5024048/placebo and/or Pegasys/Copegus. Virologic breakthrough is defined as:

A sustained increase in HCV RNA of  $\geq 1 \log_{10}$  IU/mL ( $\geq 2$  consecutive measurements) while on boceprevir/RO5024048 compared with the on-treatment nadir (where the nadir is a  $\geq 1 \log_{10}$  IU/mL decrease from baseline after 2 weeks of treatment or  $\geq 2 \log_{10}$  IU/mL decrease from baseline after 4 weeks of treatment)

Confirmed quantifiable HCV RNA ( $\geq 25$  IU/mL by  $\geq 2$  consecutive measurements) in a patient who had been previously confirmed as having unquantifiable HCV RNA ( $< 25$  IU/mL by  $\geq 2$  consecutive measurements) before the end of treatment with boceprevir/RO5024048

Response ( $< 25$  IU/mL by  $\geq 2$  consecutive measurements) to boceprevir/RO5024048 treatment and subsequent quantifiable viral load ( $\geq 25$  IU/mL by  $\geq 2$  consecutive measurements) once boceprevir/RO5024048 treatment has been completed (but Pegasys/Copegus treatment continues)

- Hepatitis C virus partial response before the end of treatment with boceprevir/RO5024048/Pegasys/Copegus/placebo, defined as an initial HCV RNA decline ( $\geq 1 \log_{10}$  IU/mL decrease from baseline after 2 weeks of treatment or  $\geq 2 \log_{10}$  IU/mL decrease from baseline after 4 weeks of treatment) followed by stabilization ( $\geq 2$  consecutive measurements similar to those at nadir) while on boceprevir/RO5024048/Pegasys/Copegus/placebo treatment and/or a HCV RNA  $\geq 1000$  IU/mL by the end of boceprevir/RO5024048/Pegasys/Copegus/placebo treatment of at least 4 weeks in duration
- Any confirmed Grade 4 laboratory abnormality deemed clinically significant (based on the investigator's assessment)
- A positive troponin value ( $> 0.100$  ng/mL)

RO5024048 should be stopped for individual patients for any of the following reasons:

- A creatinine clearance decrease  $\geq 35\%$  from baseline or  $< 60$  mL/min ( $< 1.00$  mL/sec) confirmed by repeat test, preferably within 1 week
- A urine protein/creatinine ratio  $\geq 0.5$  (56.51 mg/mmol) and greater than the baseline value confirmed by repeat test, preferably within 1 week (see [Appendix H](#))

Refer to [Appendix F](#) and [G](#) for more details on stopping rules and for additional guidance on the management of specific AEs and laboratory abnormalities.

Patients who discontinue study drug prematurely will be asked to return to the clinic for a Study Completion/Early Termination Visit (see Section [4.5.2.3](#)) and may undergo follow-up assessments (see Section [4.5.2.4](#)). The primary reason for premature study drug discontinuation should be documented on the appropriate eCRF. Patients who discontinue study drug prematurely will not be replaced.

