##### **4.5.1.1      Efficacy Assessments**

Serum HCV RNA will be assessed in all randomized patients by polymerase chain reaction (PCR) techniques using the Roche COBAS TaqMan HCV v2.0 Test (less than the LLOQ; < 25 IU/mL).

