## Patient Identification for Resistance Analysis

Samples will be selected for sequence determination of the NS3 protease and NS5B coding region(s) from patients experiencing (for the purposes of sequence determination an HCV RNA  $\geq 1000$  IU/mL is required):

1. Virologic breakthrough
  - a) Those patients who show either a sustained increase in HCV RNA of  $\geq 1 \log_{10}$  IU/mL ( $\geq 2$  consecutive measurements) while on boceprevir/RO5024048 compared with the on-treatment nadir (where the nadir was a  $\geq 1 \log_{10}$  IU/mL decrease from baseline after 2 weeks of treatment)
  - b) Those patients with confirmed quantifiable HCV RNA ( $\geq 25$  IU/mL by  $\geq 2$  consecutive measurements) in a patient who had been previously confirmed as having unquantifiable HCV RNA ( $< 25$  IU/mL by  $\geq 2$  consecutive measurements) before the end of boceprevir/RO5024048 treatment
  - c) Those patients who responded ( $< 25$  IU/mL by  $\geq 2$  consecutive measurements) to boceprevir/RO5024048 treatment and who have subsequent quantifiable viral load ( $\geq 25$  IU/mL by  $\geq 2$  consecutive measurements) once boceprevir/RO5024048 treatment has been completed (but Pegasys/Copegus treatment continues).
2. Partial response. Those patients who show an initial HCV RNA decline (a  $\geq 1 \log_{10}$  IU/mL decrease from baseline after 2 weeks of treatment) followed by stabilization ( $\geq 2$  consecutive measurements similar to those at nadir) while on boceprevir/RO5024048 treatment and/or experience a HCV RNA  $\geq 1000$  IU/mL by the end of boceprevir/RO5024048 treatment of at least 4 weeks in duration
3. Non-response. A decrease in HCV RNA of  $< 1 \log_{10}$  IU/mL from baseline after 2 weeks of treatment
4. Relapse. Patients who responded to boceprevir/RO5024048 treatment and have subsequent quantifiable viral load ( $\geq 25$  IU/mL by  $\geq 2$  consecutive measurements) once all treatment has been completed.

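### The virologic stopping rules in Protocol 4.6.1.1 contradict themselves and Appendix F: read literally, one stops drug in suppressed patients, and the two Week 24 bullets are not two workable rules

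*Protocol*

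**What the plan says.** Section 4.6.1.1 introduces its list with "All study medications should be stopped for individual patients for any of the following reasons". Four virologic entries matter here.

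- First Week 24 bullet: "Hepatitis C virus RNA titer > 100 IU/mL by Week 24".
- Second Week 24 bullet: "Quantifiable HCV RNA at Week 24". Section 4.5.1.1 sets the assay limit ("less than the LLOQ; < 25 IU/mL"), so quantifiable means 25 IU/mL or more.
- Breakthrough: one definition needs confirmed quantifiable RNA "in a patient who had been previously confirmed as having unquantifiable HCV RNA". Another labels two or more consecutive values below 25 IU/mL a response and then describes its loss.
- Partial response: a fall of at least 1 log10 after 2 weeks or at least 2 log10 after 4 weeks, then stabilization, meaning at least two "consecutive measurements similar to those at nadir) while on boceprevir/RO5024048/Pegasys/Copegus/placebo treatment". This is joined by 'and/or' to a second limb, HCV RNA of at least 1000 "IU/mL by the end of boceprevir/RO5024048/Pegasys/Copegus/placebo treatment of at least 4 weeks in duration".

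Three other places bear on the reading:

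- Section 4.5.1.8 (patient identification for resistance analysis) gives nearly the same definition of partial response, without the 4-week route. It adds that "for the purposes of sequence determination an HCV RNA" of at least 1000 IU/mL is needed.
- The opening paragraph of Appendix F says that patients who respond are meant to stay on drug until the treatment period is complete.
- Sections 3.1 (Table 1), 4.1 and 4.3.2 fix the planned regimens: RO5024048 for 24 weeks, and the other drugs for 24 weeks (Arm A) or 48 weeks (Arm B).

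**The concern.** A mandatory all-drug stop has to classify each viral-load course in one way only. Here a patient suppressed below 25 IU/mL at consecutive visits is a responder under the breakthrough definitions and, on the literal text, a partial responder who must stop. Appendix F points the other way. The two Week 24 bullets carry different thresholds and different prepositions, and nothing says how they relate.

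This matters for estimation because SVR-12 is timed from the actual end of treatment (6.4.1). The stopping rules therefore set both the duration that is evaluated and which Arm B patients continue beyond Week 24, which is the planned difference between the arms. Patients who stop early are not replaced (4.6.1.1), and reasons for early discontinuation are tabulated by arm (6.2). If sites applied the text differently, both the delivered durations and those tables would reflect the difference.

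**Working it through.** **1. The plan's own figure.** Section 6.1 gives a 90% interval of ±15% with 30 patients per arm at 45% to 55% response. The Wald half-width is 1.645 × √(p(1−p)/30). At p = 0.45 or 0.55 it is 1.645 × √(0.2475/30) = 0.149, and at p = 0.50 it is 0.150. The stated figure reproduces. Exact Clopper–Pearson half-widths for 13 to 17 responders are 0.160 to 0.161. Nothing below changes the sample size.

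**2. The plateau limb.** 'And/or' makes stabilization sufficient without the 1000 IU/mL limb, and stabilization carries no lower bound. A patient who stays below 25 IU/mL sits at nadir on every later visit, so the limb is met.

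To see when, the rule was applied literally to the Appendix A visits (Weeks 1, 2, 4, 8, 12, 16, 20, 24, 30, 36, 42, 48). The following are assumptions, not protocol figures: baseline 6.5 log10 IU/mL; 'similar' means within 0.3 log10; suppression is maintained once reached; two further visits are needed after the nadir visit. Planned weeks lost are 24 or 48 minus the stop week.

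| First visit < 25 IU/mL | Rule met, Arm A | Planned weeks lost, A | Rule met, Arm B | Planned weeks lost, B |
|---|---|---|---|---|
| Week 2 | Week 8 | 16 | Week 8 | 40 |
| Week 4 | Week 12 | 12 | Week 12 | 36 |
| Week 8 | Week 16 | 8 | Week 16 | 32 |
| Week 12 | Week 20 | 4 | Week 20 | 28 |
| Week 16 | Week 24 | 0 | Week 24 | 24 |
| Week 20 | not met before planned end | 0 | Week 30 | 18 |

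For responders suppressed by Week 16, a literal stop falls at the same visit in both arms, so their planned difference in duration would vanish. As a diagnostic only, and not as a proposed rule: if only quantifiable values counted towards the plateau, none of these courses would meet it. The missing condition is therefore what creates the conflict.

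**3. Exposure.** 0.45 × 30 = 13.5 and 0.55 × 30 = 16.5 expected sustained responders per arm. Patients suppressed on treatment who relapse later would also be exposed.

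**4. The Week 24 bullets.**

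- 'By' means at Week 24: any value above 100 is also at least 25, so the first bullet is a subset of the second and adds no patient.
- 'By' means not yet down to 100 by Week 24: the Week 24 value is then above 100, hence at least 25, and the bullet again adds no patient.
- 'By' means any value up to Week 24: entry requires at least 50,000 IU/mL (4.1.1, criterion 4), so every eligible patient meets it at baseline.
- The same, counting on-treatment values only: a patient escapes only by reaching 100 or less at the Week 1 visit and never exceeding it again. That needs a fall of log10(50,000/100) = 2.70 from the entry minimum, or 4.0 to 5.0 log10 from assumed baselines of 10^6 to 10^7. The protocol gives no Week 1 kinetics, so the share caught cannot be stated.

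None of these readings yields two distinct, workable rules.

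**The case against.** The best defence is that the intent is recoverable. The bullet is labelled partial response, and the same list uses response for confirmed values below 25 IU/mL. The breakthrough definitions for patients who were suppressed and then rebound would be largely empty if suppression itself ended treatment. Section 4.6.1.1 refers to Appendix F for more on stopping rules, and Appendix F keeps responders on drug. Elsewhere partial response is handled as failure, with a confirmatory sample and referral to the resistance study. An investigator would probably not stop a suppressed patient, and no evidence shows that sites would diverge. All of this stands as a reason not to predict stops. It does not make the text correct, because a mandatory rule should not work only when its wording is overlooked.

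Two further points stand. The 1000 IU/mL requirement in 4.5.1.8 is stated to be for sequencing. It selects samples and is not part of the clinical definition, so it does not show that 4.6.1.1 dropped a clinical condition. A redundant Week 24 bullet changes no patient's treatment, and the any-value reading is unworkable enough that no site could run the trial on it. Because Week 24 is Arm A's planned end, a rule applied at that visit affects continuation in Arm B only.

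A reader might infer that the regimens being estimated are undefined. They are not: drugs, doses and planned durations are stated, and patients are analyzed as randomized (6.4).

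**Conclusion.** The point holds as a contradiction within 4.6.1.1 and between it and Appendix F. Read literally, the plateau limb orders all drugs stopped in patients maintained below 25 IU/mL, whom the same section calls responders. The two Week 24 bullets are either redundant or, on the any-value reading, met before treatment starts. What is left ambiguous is the stopping component, and so the actual treatment duration from which SVR-12 is counted, including which Arm B patients continue after Week 24.

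The size is about 13.5 to 16.5 of 30 patients per arm exposed to the wording, at the protocol's assumed 45% to 55% SVR. A reader might take that as the number who would lose treatment; the documents do not support this. It is expected SVR multiplied by arm size. The timing in the table rests on assumed kinetics and on the undefined word 'similar', and late-suppressed Arm A patients reach their planned end first or at the same visit. Nor do the documents support saying that the 100 IU/mL bullet stops nearly everyone at the first treatment visits. Only the baseline case is certain, and that reading is implausible in practice. This is a text error to correct, not a flaw in the design or sample size.

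**What to change.** Reconcile the entries of 4.6.1.1 with one another and with the intention stated in Appendix F, and align the definition of partial response with 4.5.1.8, including the 4-week route that only 4.6.1.1 contains. The test of the result is that no HCV RNA course counts as both response and partial response. Reconcile the two Week 24 bullets so that each has one unambiguous meaning and their relation is clear. The clinical team decides the thresholds, the timing and which rules remain. Use the single reconciled text for site instructions and for classifying reasons for discontinuation.

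The cost is one paragraph in an amendment and a letter to sites. No extra data, visits or patients are needed. The change is comparable in scale to Amendment F, which corrected one omitted visit.
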